### Wound healing trajectory definitions

A normal healing trajectory is considered a reduction in wound surface area of 10–15% per week, or at least 30% over a 2-week period. Wounds that fail to decrease in size by 30% over the first 2 weeks of treatment have a 68% probability of failing to heal within 24 weeks [51]. Ulcer area reduction at 2 weeks predicts failure to heal by 24 weeks in the venous leg ulcers of patients living alone. Overall time to closure depends on wound size and characteristics, patient age, nutritional status, comorbid conditions, adherence to treatment, and additional factors to be explored in this study. While there is no wound severity score for venous leg ulcers (unfortunately there is no staging or classification score for these types of wounds similar to staging criteria for pressure injuries), consensus on severity among wound care experts is emerging and is based on wound clinical characteristics as follows:
Grade 3 = size > 10 cm^2^, infection/biofilm/osteomyelitis, ulcer > 4 weeks without change in size, high exudate, pain > 7 numeric rating scale (NRS), necrotic debris debris/fibrin covering > 50% of wound bed, odor, periwound inflammation/maceration, large lower extremity edema based on calf circumference - would require Level 1 treatment approaches (see below);Grade 2 = size 5–10 cm^2^, critically colonized, moderate exudate, pain 4–6 NRS, necrotic debris/fibrin 25–50%, moderate lower extremity edema - would require Level 2 treatment; and,Grade 1 = size < 5 cm^2^, light exudate, pain < 4 NRS, necrotic debris/fibrin < 25% or > 75% pink granulation tissue, mild lower extremity edema – would require Level 3 treatment.

Healing is determined by consistent reduction in size and symptoms and presence of epidermis covering 100% of wound bed. There are treatment differences depending on wound characteristics such as drainage, necrotic debris, leg edema, and infection. We will account for changes in grade and treatment by treatment types (levels) in our analyses as follows:
Level 1: inelastic, multi-component, high compression [> 40 mmHg], mechanical/sharps debridement, antibiotics, advanced healing technologies such as skin substitutes, hyperbaric oxygenation;Level 2: moderate compression [30–40 mmHg], exudate management, enzymatic debridement; and,Level 3: moderate compression, moist healing environment.

#### Sample size considerations

With 28 participants per group we will have 80% power to detect an effect size of 0.6 standardized units effect size between the 2 groups, assuming 2 post-baseline time points; intra-class correlation no greater than 0.4; level of significance [α] = 0.05, two-tailed. Assuming standard deviation (sd) = 2, this translates into a raw effect size (difference in change scores) of 1.2. If the pooled sd is 5 units, the standardized effect size is equivalent to a raw detectable difference in change scores between the groups of 4.5 raw scale units. We will enroll 10 males and 10 females prior in each group so that we can complete thorough data analysis for outcome comparisons by sex. If necessary we will over enroll to achieve 28 participant per group at V3. The distribution of patients at one of our main wound centers is 60.0% male, 40.0% female; 60.0% African American, and 40.0% White with mean age 70 years.

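### The detectable raw difference given for SD 5 (4.5 units) contradicts the stated 0.6 SD effect, which gives 3.0 units

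*Protocol article*

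**What the plan says.** The paragraph under Sample size considerations in the protocol article opens with a single standardised effect: "With 28 participants per group we will have 80% power to detect an effect size of 0.6 standardized units". The conditions attached are "assuming 2 post-baseline time points", "intra-class correlation no greater than 0.4" and "level of significance [α] = 0.05, two-tailed".

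Two conversions to raw units follow. The first reads "Assuming standard deviation (sd) = 2, this translates into a raw effect size (difference in change scores) of 1.2". The second begins "If the pooled sd is 5 units, the standardized effect size is equivalent to" and ends with "a raw detectable difference in change scores between the groups of 4.5 raw scale units".

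The second sentence speaks of the standardised effect size as already defined, and 0.6 is the only one in the article. Both sentences describe the same quantity, a between-group difference in change scores. No separate SD of change and no second effect size is given.

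**The concern.** A standardised effect becomes a raw difference by multiplying it by the SD. The article does this correctly for SD 2, and the same step for SD 5 does not give 4.5. Two adjacent sentences that should express one sensitivity on two scales therefore disagree.

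Aim 1 compares the groups on a series of questionnaire scores, and the raw detectable difference is how a reader judges whether 28 per group is enough on such a scale. With 4.5 printed, differences between 3.0 and 4.5 units on a scale with SD 5 look too small for the study to find with 80% power, although the preceding sentences claim that 0.6 SD, which is 3.0 units, can be found. The Discussion says that the small sample may miss statistically significant differences and that clinically relevant differences will be looked for, so the stated sensitivity bears on how a null result is read.

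**Working it through.** **Inputs**, all from Sample size considerations: standardised effect 0.6; 28 per group; 80% power; two-sided α 0.05; two post-baseline time points; intra-class correlation (ICC) at most 0.4; SD 2 with raw difference 1.2; SD 5 with raw difference 4.5.

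**1. The plan's own conversion.** Raw difference = standardised effect × SD.

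- SD 2: 0.6 × 2 = 1.2. This agrees with the text and confirms the rule in use.
- SD 5: 0.6 × 5 = 3.0. The text has 4.5, and 4.5 / 3.0 = 1.5, so it is 50% too large.

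**2. What 4.5 would imply.**

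- With SD 5: 4.5 / 5 = 0.9 SD.
- With effect 0.6: 4.5 / 0.6 = SD 7.5.

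**3. Could SD 5 be the SD of a single score, converted to the SD of a change score?** With correlation ρ between visits, the SD of a change is SD × √(2(1 − ρ)).

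- ρ = 0.4: 0.6 × 5 × √1.2 = 3.29.
- ρ = 0: 0.6 × 5 × √2 = 4.24.
- To reach 4.5: √(2(1 − ρ)) = 4.5 / 3.0 = 1.5, so 2(1 − ρ) = 2.25 and ρ = −0.125.

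A negative correlation between repeated scores in the same person is implausible. This reading would also spoil the SD 2 example, which is a plain product.

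**4. Could some repeated-measures model make 0.9 SD the detectable effect?** The article does not say which model lies behind the calculation, so several were tried. Let v be the variance of the analysed summary relative to that of one measurement. The detectable effect at 80% power is (1.960 + 0.842) × √v × √(2/28) by the normal approximation. Power and n per group below are from the two-sample t-test, at ICC 0.4.

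| Analysed summary | v | Detectable effect (SD) | Power at 0.6 SD | Power at 0.9 SD | n per group, 80% power at 0.9 SD |
|---|---|---|---|---|---|
| Mean of 2 post-baseline, baseline-adjusted | 0.54 | 0.55 | 85.1% | 99.4% | 12 |
| Mean of all 3 visits | 0.60 | 0.58 | 81.2% | 99.0% | 13 |
| Mean of 2 post-baseline | 0.70 | 0.63 | 75.0% | 97.7% | 15 |
| Mean of 2 post-baseline minus baseline | 0.90 | 0.71 | 64.2% | 93.6% | 19 |
| Single measurement | 1.00 | 0.75 | 59.7% | 91.1% | 21 |
| Single change score | 1.20 | 0.82 | 52.1% | 85.5% | 25 |

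The mean of all three visits reproduces the stated design closely: 81.2% power at 0.6 SD with 28 per group. No row has a detectable effect as large as 0.9 SD. A lower ICC does not help in the models that average visits without subtracting baseline, because it lowers the detectable effect further (0.43 SD for the mean of three visits at ICC 0).

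**The case against.** The strongest reply is that the wrong number is only the second of two illustrations. The sample size rests on 0.6 SD, 80% power, the ICC and α, and neither SD enters it. Correcting 4.5 changes no sample size, endpoint, model or decision rule. The error also makes the study look less sensitive than claimed, so it does not flatter the design. Neither SD is tied to a named instrument, and the article gives no minimally important difference against which 4.5 would be read. A reader can see the right conversion one sentence earlier. All of this stands, and it limits the consequence of the error. It does not make 4.5 correct.

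A second reply is that any power figure attached to 0.9 SD depends on a model the article does not specify. That is also right, so a range is given here. The contradiction itself needs no power model, because it rests on 0.6 × 5 alone.

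A third is that the article cannot show which number was mistyped. The 4.5 may come from an SD of 7.5, or from another calculation with an effect of 0.9. This stands too, and the correction is conditional for that reason.

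**Conclusion.** The figure is wrong as written. With the stated effect of 0.6 and SD of 5, the only value that follows is 3.0 raw units, and the printed 4.5 exceeds it by 1.5 units, or 50%. Nothing else in the article supplies an effect of 0.9, an SD of 7.5 or another conversion that would justify it.

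If 4.5 at SD 5 were taken at face value, 28 per group would give about 86% to 99% power, and 12 to 25 per group would be enough for 80%. Those ranges assume an ICC of 0.4 and that SD 5 is the SD of a single score, and they cover the models tabulated above. The practical weight is limited: the slip does not alter 28 per group or the claim of 80% power at 0.6 SD. It is still a definite numerical error in the sample-size justification, in the form of the result that readers are most likely to use.

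**What to change.** Ask the authors to confirm the intended effect size and SD, then make the sentence consistent with them:

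- If 0.6 and SD 5 both stand, replace 4.5 with 3.0.
- If the SD was meant to be 7.5, keep 4.5 and correct the SD.
- If 4.5 was carried over from a calculation with an effect of 0.9, it does not belong beside the 0.6 statement and should be replaced with 3.0.

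The cost is one number in one paragraph. Recruitment, the sample size, the analysis and the conduct of the study are unaffected.

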### Data and safety monitoring

Considering the study design and specific procedures to be performed, the overall risk level for enrolled participants is considered to be minimal. Accordingly, this study will employ the use of an Independent Safety Monitor (Board cerified D.O.) who will be provided with real-time electronic access to participant data. This physician will be responsible for reviewing and grading adverse events, monitoring the study safety profile, and making recommendations to the Principal Investigor regarding study modification, termination, and continuance.

## Discussion

There is a critical need to understand the trajectory of wound healing and interrelated psychosocial factors in lonely persons with CVLUs and to differentiate molecular mechanisms to advance future treatment approaches aimed to improve chronic wound healing and quality of life. We have demonstrated considerable expertise on the phenomenon of loneliness and its relation to health for chronically ill adults in the U.S. in analyses of Health and Retirement Study (HRS) data that identified predictors and outcomes of loneliness [52, 53] incorporated into the psychoneuroimmunological (PNI) conceptual model (Fig. 2).

**Fig. 2 Fig2:**
[figure not shown]
Conceptual model of Key Study Variables Mapped to Major Concepts of the Psychoneuroimmunological (PNI) Paradigm. Note: Variables included in this model were derived from results of preliminary studies and findings from the scientific literature on loneliness and chronic venous leg ulcers

Descriptive studies of loneliness in adults in Appalachia with chronic illness have reported loneliness correlated with depression (*r* = .388, *p* < .05), lower quality of life scores (*r* = .272, *p* < .05), and diminished social support (*r* = .274, *p* < .05), particularly diminished emotional support (*r* = .459, *p* < .01) [54]. Studies of stroke survivors discovered that loneliness was correlated *(p* < .05) with poorer quality of life on 13 domains from the Neuro-QoL [55, 56] and in systematic reviews, relationships were explicated between loneliness and multiple chronic conditions, providing evidence that loneliness may have higher prevalence in rural-residing individuals and that interventions are needed for loneliness in this population [17]. Further, recent qualitative work has discovered that the emotions of worry, anger, and fear are present for lonely older women and that lonely stroke survivors have unmet connection needs [47, 57]. A funded study led to the development of LISTEN, a novel intervention for loneliness that has been deemed feasible, acceptable, and initially effective for diminishing loneliness, and concurrently, diminishing measures of inflammation as persons became less lonely [58]. Finally, in a study of gene expression in lonely adults in a pilot randomized controlled trial of LISTEN, data suggest gene expression for inflammation and immunity changed in a favorable hypothesized direction [59]. The team spent extensive time identifying which variables to include, guided by the PNI model so that we could logically determine a gene expression profile in people with wounds, building on the current evidence base. Note also that previous research on gene expression in the HRS sample has also verified the association of loneliness with increased CTRA gene expression in older adults [60].

Previous research in social genomics has linked adverse social conditions to increased expression of pro-inflammatory genes in correlational human studies, in experimental animal and human models showing causal effects, and in cellular model systems dissecting the specific molecular signaling pathways involved [39, 43]. Loneliness in particular has been repeatedly linked to up-regulated expression of pro-inflammatory genes (i.e., *IL1B, IL6, IL8, TNF*), and down-regulated expression of genes involved in innate antiviral responses (*IFNB, IFIs, MX, OAS*) [18, 60–66]. This recurring pattern appears to reflect the activation of CTRA in myeloid-lineage immune cells [39, 67]. Our in-depth review of the literature guided the selection of these genes and is based on the best available data. We believe the novelty is in the application of the gene analysis to a population that suffers with wounds. However, the impact of this biomarker profile on chronic wound healing remains unstudied.

We have identified several challenges to our study including relevance of selected biomarkers, models to assess healing, sample size, generalizability of results, and racial/ethnic composition. Increased expression of inflammatory markers is associated with a variety of factors such as older age, multiple chronic conditions (obesity, diabetes), pain, smoking, lower socioeconomic status, and poor functional status [68–70]. We recognize the majority of individuals with CVLUs is generally older (≥60 years of age), has high functional impairment, poor quality of life, and multiple chronic conditions. However it is not known whether there is a distinct profile in patients with chronic wounds and in particular those with loneliness. We will account for these co-variates in our analyses.

Currently there is no assessment mechanism available to predict healing that includes an inflammatory biomarker or psychosocial variables such as loneliness and social isolation. If relationships are indicated among our study variables (and confirmed subsequently), these factors could be added to currently available disease-specific risk factor models to predict non-healing in wound populations. The M.A.I.D. score, predominantly used in wound care, was created out of 4 clinically-defined parameters to estimate long-term clinical outcomes [71]. However, there are no psychosocial, physical or biological components in this score, thus it lacks full scope risk factors for accurate prediction.

We recognize the small sample size may not allow for detecting statistically significant differences; however, as the focus of the exploratory aim is to generate hypotheses rather than to confirm, we will be able to establish preliminary relationship profiles among the psychosocial stressors and symptom variables. In addition, we will investigate whether there is an indication for clinically relevant differences that support further focused exploration in future studies.

We acknowledge generalizability of the anticipated results is limited in this small exploratory study and anticipate, in a future trial, we will have an adequately powered study and a greater diversity (Latinx) of participants. To this end, we will develop study materials, for example, in Spanish to reflect the diversity of the population.

The projected racial and ethnic composition of the participant sample is a concern given the established differences in gene expression among and between these groups; it is unlikely that the least frequent groups (e.g., Hispanic) can be properly evaluated in the proposed analyses, impacting on rigor. We agree and acknowledge the concern about the differences in gene expression among various ethnic/racial groups; for this small exploratory trial, we are focused on fidelity to our PNI model. Though it is not the primary aim of this observational study to determine ethnic differences, we have included age, sex, and race and ethnicity as individual person factors based soundly in the PNI model and these variables will be included and accounted for in preliminary analyses.

## Conclusion

Our study addresses a highly prevalent clinical problem - chronic venous leg ulcers (CVLUs) that affect millions of individuals worldwide, causing considerable suffering, disability and poor quality of life. The objective of this exploratory project is to assess stressors, symptoms and biomarkers associated with lonely and non-lonely individuals with CVLUs. Findings are expected to improve understanding of molecular mechanisms common to loneliness and inflammation towards development of a biopsychosocial prognostic indicator of healing potential in persons with chronic wounds. If differences in the biomarker profile of L+ individuals and CVLUs are found, further exploration of co-variates could form the bases of a new type of assessment that could potentially predict nonhealing.

## Data Availability

The datasets used and/or analyzed during the current study will be housed and stored at the Medical University of South Carolina in accordance with the academic institution’s Records Retention policy. Data will be made available from the corresponding author on reasonable request after publication of the results on the main research questions.

## Abbreviations

CVLUs: Chronic venous leg ulcers
CTRA: Conserved transcriptional response to adversity
HPA: Hypothalamic-pituitary adrenocortical
HRS: Health and Retirement Study
L-: Without loneliness
L +: With loneliness.
LISTEN: Loneliness Intervention using Story Theory to Enhance Nursing sensitive outcomes
M.A.I.D.: Palpable pedal pulses (I), Wound area (A), Ulcer duration (D), and Presence of multiple ulcerations (M)
MEM: Mixed effects models
NRS: Numeric rating scale
PNI: Psychoneuroimmunological
sd: Standard deviation
